### Power calculations

Following Libby et al. [25], a sample of 60,000 subjects (20,000 randomized to the usual pre-notification letter group, 20,000 randomized to the HLOC Group and 20,000 to AR group) would enable an increase in FOBT uptake of between 3% and 5% to be detected in all social deprivation groups with 80% power at the 5% level.

### Evaluation

The effects of the intervention will be evaluated in all participants via measurement of the primary and secondary outcome variables listed above.

#### ***Process evaluation***

As this study is based on a one-off questionnaire no process evaluation is required.

### Timetable

This is a 20-month project. Months 1–6 will be spent designing, piloting and finalising the exact layout of the questionnaires and updating the IT system with the variables required for the current research. During months 5–6 we will also finalise the mailing procedures and obtain PAC (Privacy Advisory Committee) approval for the data linkage. The questionnaire packs will be posted out to participants commencing in month 7. The Scottish Bowel Screening Centre estimate that approximately 2,500 pre-notification letters are sent out each day, thus it will take approximately 5–6 weeks to send out 40,000 questionnaires (treatment arms 2–3), plus 20,000 pre-notification letters (treatment arm 1).

Participants can return their FOBT test kit at any point over the following 6 months; therefore we will have a 6-month follow-up period. During months 8–14 the questionnaire returns will be scored as they are returned, and entered into the SPSS study spreadsheet, and the analytic strategy will be finalised. The data extract will be carried out at the end of month 14. Months 15–18 will be spent collating the FOBT returns with the questionnaire scores, and performing the logistic regression and mediation analyses. In months 19–20 we will draft scientific papers, conference presentations and the Chief Scientist Office final report.

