### Recruitment

Following the method of Libby et al. [25], participants will be a randomly recruited representative sample of all participants in the national colorectal screening programme in Scotland. Participants will be sampled from all residents aged 50–74 years who have a Community Health Index Number (a unique patient identifier) that is associated with an NHS Board. As a result of the findings of Libby et al. [25], the programme now sends all eligible people a standard pre-notification letter 2 weeks before being sent a FOBT by post, which they are required to complete at home and then return to the laboratory at the Scottish Bowel Screening Centre in Dundee for analysis. Our questionnaires will be included along with this pre-notification letter.

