### Analysis

Our primary analysis will be chi-square tests to explore the proportion of respondents who return the test kits within 6 months as a function of the 3 arms (control, HLOC or AR). Logistic regression will be used to examine screening uptake by treatment arm, controlling for potential between-arm differences in age, gender and social deprivation, whether a reminder letter was sent, number of previous FOBT returns, and previous failures to return. Our primary analysis will be on an ‘Analysed as Allocated’ basis, i.e. including all participants randomised to treatment arms, whether they return a questionnaire or not. Secondary analysis will be conducted on the questionnaire respondents (HLOC and AR groups only), to test the mediating role of intention, AR, health locus of control, disgust and perceived benefit in influencing FOBT returns.

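### The mediation analysis takes all questionnaire respondents, with no recorded receipt date or cut-off to show that the answers came before the kit was returned

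*Protocol article*

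**What the plan says.** All references are to the protocol article.

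- **Mailing order (Recruitment).** On the kit: "the programme now sends all eligible people a standard pre-notification letter 2 weeks before being sent a FOBT by post". On the study material: "Our questionnaires will be included along with this pre-notification letter". The questionnaire therefore leaves two weeks ahead of the kit.
- **Collection (Timetable).** "The questionnaire packs will be posted out to participants commencing in month 7". Then: "Participants can return their FOBT test kit at any point over the following 6 months; therefore we will have a 6-month follow-up period". For the questionnaires: "During months 8–14 the questionnaire returns will be scored as they are returned". There is one extract: "The data extract will be carried out at the end of month 14".
- **Analysis set (Analysis).** "Secondary analysis will be conducted on the questionnaire respondents (HLOC and AR groups only), to test the mediating role of intention, AR", together with health locus of control, disgust and perceived benefit. No condition on when the questionnaire was completed or received is attached.
- **Data handling (Sampling and randomisation).** Questionnaires are linked by a unique identifier to a kit return that the text describes as coming later. The only checks named at data entry concern valid values and ranges.
- **Use of the answers (Research questions; HLOC Intervention).** Research question 4 asks whether these beliefs influence uptake, and a high chance locus of control score is expected to predict lower return.

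**The concern.** A mediator or predictor has to come before the outcome it is meant to explain. The text treats the questionnaire as coming first, but nothing it fixes about collection or the analysis set secures that order. A person can receive both mailings, post the kit, and then fill in the questionnaire. That person's stated intention, perceived benefit, disgust and (in the anticipated regret arm) regret are then reported in the light of having done the test.

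Someone who has already returned the kit would plausibly state high intention and benefit and low disgust. The associations with kit return would then look stronger than they are, and part of an apparent mediating pathway could run from behaviour to belief. These are the quantities that research question 4 and the mediation analysis report. A large respondent sample would not remove the bias.

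**Working it through.** **1. Do the two return periods overlap?** Take posting to begin at the start of month 7 (an assumption; the text gives only the month) and mailing to last the stated 5–6 weeks.

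- First kits go out 2 weeks after the first letters: week 2, within month 7.
- Last kits go out 2 weeks after the last letters: weeks 7–8. At 4.35 weeks per month this is 7/4.35 = 1.6 to 8/4.35 = 1.8 months, so before the end of month 8.
- Six months later is before the end of month 14, which agrees with the extract date.

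Kit returns can therefore arrive from month 7 to month 14. Questionnaire scoring in months 8–14 lies inside that period.

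**2. Does any stated rule restore the order?** The mailing lead sets the intended order but does not enforce it. The entry checks named do not involve dates. The respondent set has no timing condition. No receipt date, closing date or comparison with the kit date appears in the article.

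**3. How large could the effect be?** The plan gives no figure on this point, so there is none to reproduce. Two illustrations follow; all their inputs are assumptions.

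*Graded model.* Intention is scored 1–7 (normal, mean 5.8, SD 1.3, rounded and capped). The logit of kit return is −1.0 + 0.35 × intention, so the true odds ratio per point is exp(0.35) = 1.42 and uptake is 72%. A share f of kit returners answer late and all then score 7. Refitting the logistic model gives:

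| f | Odds ratio per point |
|---|---|
| 0 | 1.42 |
| 2% | 1.44 |
| 5% | 1.48 |
| 10% | 1.54 |
| 20% | 1.66 |
| 30% | 1.81 |

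If late responders instead rise by one point, the odds ratio is 1.43 at f = 2% and 1.49 at f = 10%. With no true association and late answers set to 7, it is 1.05, 1.10 and 1.21 at f = 5%, 10% and 20%.

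*Binary model, no true association.* A share b of people state high intention, and late returners all do. Among returners the share is r = f + (1 − f)b, and the spurious odds ratio is [r/(1 − r)] / [b/(1 − b)]. For b = 0.5 and f = 0.10: r = 0.55, and 0.55/0.45 = 1.22. For b = 0.7 and f = 0.10: r = 0.73, and (0.73/0.27)/(0.7/0.3) = 1.16.

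| f | b = 0.5 | b = 0.7 |
|---|---|---|
| 5% | 1.11 | 1.08 |
| 10% | 1.22 | 1.16 |
| 20% | 1.50 | 1.36 |
| 30% | 1.86 | 1.61 |

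Both models push the association upward. Its size depends on f, which the article does not give.

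**The case against.** The strongest reply is that this is detail for a full protocol or analysis plan. The Timetable says the analytic strategy will be finalised in the same months, before the extract, and a timing rule could be added then. That is fair for the choice of analysis. It does not cover data capture: a receipt date has to be noted when the envelope arrives, and a later decision cannot be relied on to recover it. The article also does more than stay silent, because it states both the collection period and the respondent set.

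Other objections limit the point, and they stand:

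- A reader might infer that the plan expressly accepts questionnaires throughout the six months. It does not say so. The months given are for scoring and data entry, and a long entry period need not mean a long receipt period. Late acceptance is the natural reading where no earlier closing date is given, but it is an inference.
- The two-week lead and the forward-looking wording of the items mean that many replies will probably precede the kit. Nothing in the article suggests that late completion is common.
- A reader might infer strong inflation of the odds ratios. The larger values need late shares of 20–30% and every late answer at the top of the scale. At 2–5% the shift is small.
- Health locus of control is a general belief scale, and there is no specific argument that it shifts after a kit is returned.
- A reader might infer that the trial's main result is at risk. It is not: the primary comparison and research questions 1 to 3 rest on randomised arm and kit return, not on questionnaire answers.

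**Conclusion.** The point holds for research question 4 and the mediation analysis only. As the article stands, questionnaires completed after the kit was returned would enter as predictors or mediators of that return, and no stated data item would let anyone identify them. The bias in the intention, benefit, disgust and regret associations is probably towards greater strength. That direction rests on the assumption that people who have done the test answer more favourably about it.

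The size is unknown. Under the graded model, a true odds ratio of 1.42 moves to about 1.44–1.48 at 2–5% late and about 1.54 at 10%, if all late responders score 7. The documents do not support a claim that the secondary results are seriously distorted, only that the design as described cannot rule it out.

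**What to change.** 1. Record the receipt date of each questionnaire at data entry, from the first day of mailing.
2. Obtain kit dispatch and kit receipt dates in the extract. The primary outcome is already defined by return within six months of dispatch, so kit timing should be obtainable.
3. Report how many questionnaires arrived after the person's kit. Receipt is not completion, so some of these will have been filled in earlier.
4. Pre-specify a sensitivity analysis of research question 4 and mediation restricted, for returners and non-returners alike, to questionnaires received within a fixed time of the letter, for example 14 days. A reply received before kit dispatch cannot have been written after using the kit. Treat mediation conclusions as supported only if they hold in this set.

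The set should not be defined as questionnaires received before the person's own kit. That rule can exclude only people who returned a kit, so it ties inclusion to the outcome.

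The cost is one extra date field at questionnaire entry and the kit dates in the extract. The sensitivity set will be smaller and made up of faster repliers, who may differ from other respondents. This is why it is proposed as a sensitivity analysis and not as the main result.

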## Discussion

It is estimated that a 5% increase in FOBT screening uptake could translate into approximately 11 additional cancers diagnosed per 100,000 of the target population. If a simple AR intervention leads to a significant increase in colorectal screening uptake, this would represent a rare example of a theoretically-driven, relatively simple psychological intervention that could result in earlier detection of colorectal cancer and many more lives being saved. This project has the full support of both the Scottish Bowel Screening Programme Board and the Detect Cancer Early Programme. If the current trial proves a clear advantage of the AR condition, it has the potential for implementation in the future National screening programme, e.g. by adding the AR questions to the pre-notification letter. If the results of the trial are positive, they will be communicated immediately to Scottish Bowel Screening Programme Board, who will then advise the Scottish Government Department of Health on implementation.
